#### Blinding

Clinicians performing a membrane sweep cannot be blinded, and it is not feasible to genuinely blind membrane sweeping for women. Therefore, neither clinicians administering the intervention nor women will be blinded to the group assignment. Data will be reviewed by two assessors blinded to the group allocation.

#### Intervention

Amniotic membrane sweeping is defined as the manual detachment of the inferior pole of the amniotic membranes from the lower uterine segment [22]. This is performed with consent by a clinician digitally through a circular motion during a vaginal examination. If the cervical os is closed, massage of the cervix will be accepted.

Women will initially be randomised in a 2:1 ratio to:
Membrane sweep (2) versus no membrane sweep (1)

Those allocated to the intervention group will then be further randomised in a factorial fashion to A, B, C or D (Table 1):
A.Membrane sweep at 39 weeks’ gestation onlyB.Membrane sweep at 40 weeks’ gestation onlyC.Membrane sweep at 39, 40 and 41 weeks’ gestation or until the onset of labourD.Membrane sweep at 40 and 41 weeks’ gestation or until the onset of labour

**Table 1 Tab1:** Allocation of the intervention group

	Sweeping at 39 weeks	Sweeping at 40 weeks
Single membrane sweeping	A	B
Weekly membrane sweeping (up to 41 weeks or until onset of labour)	C	D

#### Control group

Women in the control arm will not receive a membrane sweep and will receive usual care (as defined by local hospital protocols and vaginal examination to determine Bishop score only). Usual care in both sites is the same and includes women attending for routine antenatal clinic appointments monthly up to week 32, fortnightly to week 38 and weekly to week 42. Women will be offered induction of labour at approximately 41 weeks’ gestation and labour induced in most women prior to 42 weeks’ gestation. We will identify any intricacies of usual care that might be present in each site but that might not become apparent outside of a research context as part of the study through the mapping usual care pathways. Other than randomisation to an intervention group or a control group, all women will receive usual care as defined by local hospital protocols. Participating in this trial will not alter the intrapartum or postnatal care pathway for the woman or her infant.

#### Withdrawal from trial/treatment or protocol deviation post-randomisation

If a woman decides to leave the trial after randomisation, she will be withdrawn from the trial and will receive usual maternity care as defined by local hospital policy. The same strategy will be implemented for protocol violations. Randomisation will take place immediately prior to the commencement of the intervention to try and mitigate these events. The pilot trial will use intention-to-treat (ITT) data analysis. If a woman withdraws from the trial, we will try to obtain consent to collect data relevant to the study and/or routine follow-up data. Information and communications will be recorded in the trial database.

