#### Primary outcomes

The following are the outcomes relating to feasibility assessment:
Recruitment: evaluation of the number and percentage of eligible women who are recruited and randomised to the study. Assessed by study-specific checklists.Retention: evaluation of the number and percentage of eligible women who are randomised, take part in and adhere to the study protocols. Data will be extracted from routinely collected data.Adherence with the trial interventions: evaluation of adherence with the trial interventions and reasons for non-compliance assessed by study-specific checklists. Data will be extracted from routinely collected data and focus group interviews with clinicians and participants at 6 weeks post-intervention.Evaluation of the randomisation process: evaluation of effective allocation of participants to the intervention/control group assessed by study-specific checklists and evaluation of the randomisation protocol throughout the randomisation period.Evaluation of attrition rates: evaluation of attrition rates assessed by study-specific checklists. Data will be extracted from routinely collected data.Evaluation of the types of attrition: evaluation of the types of attrition assessed by case report forms. Data will be extracted from routinely collected data.Evaluation of the data collection process through study-specific checklists: evaluated, statistically and narratively, by assessing the completeness of the outcome measurements at baseline and postnatal (6 weeks) through study-specific checklists. Researchers will manually examine the data collected. They will assess the proportion of complete data collection forms, the quality of data collected and the applicability of this data in facilitating pilot trial outcomes.Estimate the main effect of individual intervention components and their interactions: estimates (with measures of uncertainty) of the main effect of individual intervention components and any interaction effect between the main effects of the embedded factorial design will be assessed and reported using regression analysis.Evaluation of the data analysis process: as this is a feasibility study, formal hypothesis testing will not be undertaken. Researchers will manually examine the data collected. Evaluation of the data analysis process will be undertaken through the assessment of gaps and limitations to the analysis process measured by study-specific checklists. Findings will be reported through descriptive statistics and graphical summaries.Evaluation of the EQ 5D: assessment of the mechanism of, timing of and delivery of the EQ 5D through study-specific checklists.Feasibility of cost analysis process through analysis of study-specific documentation: assessment of data collection tools to undertake cost-effectiveness analysis through study-specific documentation. Researchers will manually examine the data to assess the mechanism of, timing of and delivery of the cost analysis tools.Feasibility of the cost-effectiveness analyses: assessment of the mechanism and utilisation of the incremental cost-effectiveness ratio (ICER), through study-specific checklists.

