#### Statistical methods and analysis

##### Sample size for pilot trial

As this is a pilot trial and not designed to evaluate the clinical effectiveness, we will not undertake a formal power analysis for sample size. We will seek to recruit 66 women per clinical site (132 women in total) over a 6-month period beginning in July 2020. This target represents 10% of that required for the definitive trial (see below) and is greater than that recommended as the minimum sample sizes for pilot studies [33]. Data obtained from this study will inform the power analysis for a definitive trial.

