#### Criteria for progressing to the main definitive trial

The criteria for progressing to a future definitive trial are based on the primary feasibility objectives of the pilot trial. The pilot will be deemed suitable to continue to definitive trial when the following are achieved:
Recruitment
At least 30% of eligible women agree to participate in the trial and 130 women are randomised.Completeness of outcome data
Complete clinical outcome data that would be collected in the main trial collected from at least 90% of pilot trial participants.Clinician willingness to participate
At least 70% of participating clinicians within the two pilot sites agree that they would be happy to implement the MILO Study. Clinician’s views, experiences and acceptability of the MILO Study will be explored within focus group interviews.

Given the primary objective of the MILO Study is to assess the feasibility of conducting a definitive randomised controlled trial, we will evaluate recruitment and retention, adherence to the MILO protocol and reasons for non-compliance, and clinicians and women’s views, experiences and acceptability of the MILO Study. In the event the MILO Study does not meet the above criteria, these results will inform whether and how the design of the definitive trial as originally envisaged should be delivered or adapted.

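### Read literally, the protocol withdraws women with protocol violations on the same terms as women who choose to leave, which conflicts with its ITT analysis and puts their follow-up at risk

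*Protocol article*

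**What the plan says.** The section on withdrawal and protocol deviation after randomisation opens with women who choose to go: "If a woman decides to leave the trial after randomisation, she will be withdrawn from the trial", after which they receive usual maternity care. The next sentence extends this: "The same strategy will be implemented for protocol violations". Two sentences later comes the analysis principle: "The pilot trial will use intention-to-treat (ITT) data analysis". The paragraph then turns to data: "If a woman withdraws from the trial, we will try to obtain consent to collect data relevant to the study and/or routine follow-up data".

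The individual-participant list under the end-of-trial discontinuation criteria has four lines. Only the line on wrong enrolment or randomisation notes that the data are kept for analysis. The other three (withdrawn consent, a newly arising exclusion criterion or safety reason, and an unanticipated adverse event) say nothing about data.

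Under Primary outcomes, the pilot is to report adherence: "evaluation of adherence with the trial interventions and reasons for non-compliance assessed by study-specific checklists". Retention is defined as "evaluation of the number and percentage of eligible women who are randomised, take part in and adhere to the study protocols". Attrition rates and types of attrition are also listed there. One progression criterion is: "Complete clinical outcome data that would be collected in the main trial collected from at least 90% of pilot trial participants".

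**The concern.** Intention to treat needs outcomes from every randomised woman, including those whose treatment did not follow the plan. A rule that ends trial participation because of a protocol violation acts on a post-randomisation event. If it also makes further data depend on a new consent, follow-up is no longer assured for women who gave consent at entry and have not taken it back. An analysis plan can define the analysis set, but it cannot recover data that a site did not collect because it took a woman to be withdrawn.

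The harm falls on what this pilot measures. Women with violations are the ones who show where adherence fails and why. Under the literal rule, one event can count as non-adherence, as lost retention (whose definition already includes adherence), as attrition and as an incomplete record. The feasibility measures then cannot be told apart. The effect estimates meant to inform planning of the definitive trial would also rest on fewer women than were randomised.

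**Working it through.** **Comparing the sections**

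- *Rule for violations:* same strategy as for women who leave, that is, withdrawal from the trial with usual care.
- *Data after withdrawal:* an attempt to obtain consent. No outcome is assured without it.
- *Analysis:* intention to treat, which presupposes outcome data on all randomised women.
- *Discontinuation list:* data retention stated for one line of four, and protocol violations other than wrong enrolment or randomisation not listed. The list therefore does not settle the matter. One line shows why the silence matters: antepartum haemorrhage is an exclusion criterion, and when it requires admission it is also a maternal secondary outcome. A woman could be discontinued for an event the trial intends to count, with no statement that her data stay.
- *Primary outcomes:* adherence, reasons for non-compliance and attrition can be described only if these women are still observed.

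**Size against the completeness criterion**

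Inputs: the recruitment target ("We will seek to recruit 66 women per clinical site (132 women in total"), that is 2 × 66 = 132, and the 90% threshold from the progression criteria.

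- Complete records needed: 0.90 × 132 = 118.8, so 119.
- Largest number incomplete: 132 − 119 = 13.
- With the 130 women named in the recruitment criterion: 0.90 × 130 = 117, and 130 − 117 = 13, the same allowance.

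The protocol states no violation rate. Let *v* be an assumed rate and *c* the assumed share of violators whose data are still obtained, with every other woman complete. Then completeness = 1 − *v*(1 − *c*), and expected incomplete records = 132 × *v*(1 − *c*).

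| Assumed *v* | *c* = 0: incomplete | *c* = 0: complete | *c* = 0.5: incomplete | *c* = 0.5: complete |
|---|---|---|---|---|
| 5% | 6.6 | 95% | 3.3 | 97.5% |
| 10% | 13.2 | 90% | 6.6 | 95% |
| 20% | 26.4 | 80% | 13.2 | 90% |

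In whole women with *c* = 0, 13 violators leave 119/132 = 90.2% and the criterion is met; 14 leave 118/132 = 89.4% and it is not.

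**The case against.** The best defence is that withdrawal here means only the end of the trial intervention. The section heading speaks of trial and treatment together, usual care is the stated consequence, and intention to treat is stated in the same paragraph. Clinical outcomes, and the number and gestation of sweeps, are extracted retrospectively from health records, so the data exist whether or not a woman is labelled withdrawn. The protocol also randomises just before the intervention begins in order to limit such events, and it plans to record reasons for non-compliance, so it evidently expects to observe these women.

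Much of this stands. It shows that the conflict may not be intended. It does not remove it, because the text never separates stopping the intervention from stopping data collection, and a site following the words could stop both. The timing of randomisation helps only in part: allocation is at 39 weeks, groups B and D start at 40 weeks, and C and D can run to 41.

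Three stronger readings are tempting, and the documents do not support them:

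- *Violators are dropped, leaving a per-protocol set under an ITT label.* Nothing removes them from the analysis set, and nothing says that data already held are discarded. The consent sentence concerns collecting data and reaches violators only through the disputed extension.
- *Data are discarded on every discontinuation line without a retention note.* One parenthesis does not establish that.
- *Removal would differ by arm, because late-start women can labour before any sweep.* No section classes a missed sweep or labour before 40 weeks as a violation, and the schedules of groups C and D end when labour begins. No bias figure can be built on that premise.

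**Conclusion.** The point holds as a conflict in wording with a practical consequence. On its literal reading, the rule puts at risk the follow-up of women who have not asked to leave, against the stated intention-to-treat analysis and against adherence and attrition as primary feasibility outcomes.

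Its size is unknown. The allowance of 13 incomplete records in 132 is firm arithmetic. That a violation rate of about 10% exhausts it is an illustration resting on two assumptions: no data are obtained from any violator, and everyone else is complete. If half the violators give data, the limit is reached at about 20%.

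The pilot plans no formal hypothesis testing, so no confirmatory result is at stake. What is at stake is the reliability of the progression figures and of the estimates carried into the definitive trial.

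**What to change.** Reconcile the withdrawal section, the primary outcomes and the individual discontinuation list by separating the end of the allocated intervention from the end of data collection. State that:

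1. a woman with a protocol violation continues to be followed through routine records and is analysed in the group to which she was randomised;
2. only withdrawal of consent to the use of her data stops collection;
3. for every other line of the individual discontinuation list, data are retained for analysis, as already stated for wrong enrolment or randomisation.

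What care follows a violation, and when the allocated intervention ends, is for the sponsor to state; this point concerns data and analysis only.

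The cost is a change to the protocol wording, and to the consent form if it ties a violation to withdrawal. No extra visits and no change in sample size are needed.

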#### Clinician training

All necessary midwives and obstetricians will receive the MILO training programme, which will include training on how to perform a membrane sweep per trial definition and training on the study protocol to enable them to support recruitment of women to the study, answer any questions women or their partners may have, support the taking of informed consent and randomisation of women. Recruitment will be supported by on-site research midwife, and training of clinicians will be dependent on the tasks they undertake. To enhance validity, reliability and generalisability of the intervention, special consideration will be given to the training of clinicians performing a membrane sweep to ensure treatment fidelity. We will develop a standardised intervention manual, and prior to the intervention start date, all clinicians who might perform a sweep will receive the manual. In addition, all relevant clinicians will receive training in the form of a tutorial video and hands-on training from an experienced trainer. This training session will teach a standardised protocol for the intervention. Adherence to this protocol will be monitored throughout the trial by the research midwife and the trial project manager.

#### Outcome measures

We will collect the following outcome data:

#### Primary outcomes

The following are the outcomes relating to feasibility assessment:
Recruitment: evaluation of the number and percentage of eligible women who are recruited and randomised to the study. Assessed by study-specific checklists.Retention: evaluation of the number and percentage of eligible women who are randomised, take part in and adhere to the study protocols. Data will be extracted from routinely collected data.Adherence with the trial interventions: evaluation of adherence with the trial interventions and reasons for non-compliance assessed by study-specific checklists. Data will be extracted from routinely collected data and focus group interviews with clinicians and participants at 6 weeks post-intervention.Evaluation of the randomisation process: evaluation of effective allocation of participants to the intervention/control group assessed by study-specific checklists and evaluation of the randomisation protocol throughout the randomisation period.Evaluation of attrition rates: evaluation of attrition rates assessed by study-specific checklists. Data will be extracted from routinely collected data.Evaluation of the types of attrition: evaluation of the types of attrition assessed by case report forms. Data will be extracted from routinely collected data.Evaluation of the data collection process through study-specific checklists: evaluated, statistically and narratively, by assessing the completeness of the outcome measurements at baseline and postnatal (6 weeks) through study-specific checklists. Researchers will manually examine the data collected. They will assess the proportion of complete data collection forms, the quality of data collected and the applicability of this data in facilitating pilot trial outcomes.Estimate the main effect of individual intervention components and their interactions: estimates (with measures of uncertainty) of the main effect of individual intervention components and any interaction effect between the main effects of the embedded factorial design will be assessed and reported using regression analysis.Evaluation of the data analysis process: as this is a feasibility study, formal hypothesis testing will not be undertaken. Researchers will manually examine the data collected. Evaluation of the data analysis process will be undertaken through the assessment of gaps and limitations to the analysis process measured by study-specific checklists. Findings will be reported through descriptive statistics and graphical summaries.Evaluation of the EQ 5D: assessment of the mechanism of, timing of and delivery of the EQ 5D through study-specific checklists.Feasibility of cost analysis process through analysis of study-specific documentation: assessment of data collection tools to undertake cost-effectiveness analysis through study-specific documentation. Researchers will manually examine the data to assess the mechanism of, timing of and delivery of the cost analysis tools.Feasibility of the cost-effectiveness analyses: assessment of the mechanism and utilisation of the incremental cost-effectiveness ratio (ICER), through study-specific checklists.

#### Clinical outcomes

This study will also collect clinical and adverse outcome data that are likely to be collected in the future definitive trial. This is done not to evaluate the clinical effectiveness of membrane sweeping within a pilot trial but to test the outcome collection processes and to help inform the sample size estimates for and safety of a future definitive study. Data will be extracted from routinely collected data. These outcomes are as follows.

##### Primary outcome (of future definitive trial)

The primary outcome is the number of participants achieving a spontaneous onset of labour.

##### Maternal secondary outcomes

Number of participants who underwent an induction of labour: formal induction of labour using pharmacological or surgical methods.Number of participants achieving a spontaneous vaginal birth: spontaneous vaginal birth.Instrumental birth: vaginal birth which is assisted with the use of instruments.Caesarean section: birth which is achieved through the surgical procedure caesarean section.Post-partum haemorrhage ≥ 500 ml: blood loss ≥ 500mls within the first 24 h of the birth of a baby.Ante-partum haemorrhage requiring hospital admission: bleeding from the genital tract, from 24 + 0 weeks of pregnancy and before the birth of the baby.Uterine hyperstimulation with/without foetal heart rate (FHR) changes: uterine hyperstimulation defined as uterine tachysystole (more than five contractions per 10 min for at least 20 min) and uterine hypersystole/hypertonicity (a contraction lasting at least 2 min). These may or not be associated with changes in the foetal heart rate pattern (persistent decelerations, tachycardia or decreased short term variability) [31].Serious maternal death or morbidity (e.g. uterine rupture, admission to intensive care unit, septicaemia).Epidural analgesia: introduction of a local anaesthetic into the epidural space of the vertebral canal.Augmentation of established labour: the stimulation of uterine contractions using pharmacologic methods or artificial rupture of the membranes to increase their frequency and/or strength following the onset of spontaneous labour or contractions following spontaneous rupture of membranes.Pyrexia in labour: pyrexia that developed any time after the onset of labour.Uterine rupture: all clinically significant ruptures of unscarred or scarred uteri. Trivial scar dehiscence noted incidentally at the time of surgery will be excluded [31].EQ 5D-5L: EuroQol EQ 5D-5L survey instrument.

##### Neonatal secondary outcomes

Serious neonatal morbidity (e.g. seizures, birth asphyxia defined by trialists, neonatal encephalopathy, disability in childhood, proven and suspected neonatal sepsis)Apgar score < 7 at 5 minCord PH < 7.20: umbilical cord blood gas testNeonatal encephalopathy: (severity of hypoxic-ischaemic encephalopathy assessed using Sarnat staging: (i) stage 1 (mild)—hyper-alertness, hyper-reflexia, dilated pupils, tachycardia and absence of seizures; (ii) stage 2 (moderate)—lethargy, hyper-reflexia, miosis, bradycardia, seizures, hypotonia with weak suck and Moro reflexes; and (iii) stage 3 (severe)—stupor, flaccidity, small to mid-position pupils which react poorly to light, decreased stretch reflexes, hypothermia and absent Moro reflex)Perinatal death: (the perinatal period is defined as ‘commences at 22 completed weeks (154 days) of gestation and ends seven completed days after birth.’ [32])Admission to neonatal intensive care unit (NICU) or equivalent

